## Abstract

**Background:**

Whether electroacupuncture is effective for patients with polycystic ovary syndrome is still inconclusive. Therefore, this study aims to evaluate the add-on effects of electroacupuncture to conventional drugs for the treatment of polycystic ovary syndrome.

**Methods/design:**

This study is a two-center, open-labeled, randomized, controlled trial. A total of 116 eligible patients with polycystic ovary syndrome will be randomly allocated in a 1:1 ratio to the electroacupuncture plus clomiphene citrate group or to the clomiphene citrate group. Participants in the electroacupuncture plus clomiphene citrate group will receive electroacupuncture treatment in addition to clomiphene citrate capsules, whereas participants in the clomiphene citrate group will be prescribed clomiphene citrate capsules only. Electroacupuncture treatment will be performed from the fifth day of menstruation or withdrawal bleeding until the next menstruation, in three sessions per week for three menstrual cycles. The primary outcome is the ovulation rate. The secondary outcomes include the dominant follicle rate, mean number of dominant follicles, endometrial thickness, time point of ovulation, follicular size before ovulation, luteinizing hormone, estradiol level, and pregnancy rate. The measuring points for outcomes will be baseline and the completion of treatment. Any adverse events occurring during the trial process will be recorded. In addition, a quality-monitoring group independent from the research team will be set up to control the quality of the trial.

**Discussion:**

The design and methodological rigor of this trial will allow for the collection of valuable data to evaluate the effectiveness of electroacupuncture for treating polycystic ovary syndrome. Therefore, this trial will contribute reliable evidence for use in clinical decision-making in acupuncture therapy of polycystic ovary syndrome as well as to future research in acupuncture for polycystic ovary syndrome.

**Trial registration:**

Chinese Clinical Trial Registry, ChiCTR-IOR-15007358, registered on 26 October 2015

## Background

Polycystic ovary syndrome (PCOS), resulting from an imbalance of hormones, is a common disease in women. Its clinical manifestations vary, but include reproductive symptoms (hirsutism [1], infertility [2], pregnancy implications, and neonatal complications [3]) and metabolic complications (obesity [4], impaired glucose tolerance, metabolic syndrome [5], and type 2 diabetes mellitus [6]). Usually, many psychological comorbidities accompany PCOS, including depression, anxiety, moodiness, panic attacks, body dissatisfaction, eating disorders, and a lower health-related quality of life [7, 8]. As one of the common causes of anovulatory infertility, PCOS accounts for a significant proportion (40 %) of all women who receive infertility treatment [2]. More than 116 million (3.42 %) women worldwide are affected by PCOS [9]. Using the Rotterdam criteria, the prevalence has been as high as 17.8 ± 2.8 % [10].

Currently, first-line conventional therapy for infertile women with PCOS is the oral administration of antiestrogen agents (for example, clomiphene citrate). Nevertheless, from a clinical point of view, the current management of PCOS with these drugs is not always satisfactory and produces some obvious side effects. After taking clomiphene citrate, metformin, or both, 41 %, 76.3 %, and 31.6 % of women, respectively, still failed to ovulate [11]. The live-birth rate for these patients was only 22.5 % after taking clomiphene citrate, 7.2 % after taking metformin, and 26.8 % after taking both clomiphene citrate and metformin. Among pregnancies, clomiphene citrate caused multiple pregnancies in 6.0 % of the cases. Other side effects include gastrointestinal symptoms, hot flashes, and symptoms associated with ovarian enlargement and ovulation [12].

Whereas first-line conventional therapy is not satisfactory, acupuncture, as a nonpharmacological therapy, is gaining popularity. Findings from previous clinical trials suggest acupuncture may induce ovulation [13]; improve menstrual frequency [14]; and improve depression, anxiety, and health-related quality of life [15] in PCOS patients. Some of the mechanisms underlying acupuncture as a treatment for PCOS have been identified. Acupuncture is able to decrease abnormally high levels of circulating luteinizing hormone (LH), which affect the LH/follicle-stimulating hormone (FSH) ratio [14, 16], and high levels of testosterone [17]. Additionally, the low associated adverse-events rate, a low risk of multiple pregnancies, and the low cost of acupuncture have been noted [18]. However, the methodological quality of these clinical trials varies, resulting in inconclusive statements on the effectiveness of acupuncture for PCOS. In this case, we designed this two-center, open-labeled, randomized controlled trial (RCT) to evaluate the add-on effects of electroacupuncture to conventional drugs on ovulation and some sex hormones in women with PCOS.

## Methods/design

### Overview of the study design

We designed an open-labeled RCT. The interventions will be performed under ideal circumstances. Therefore, this trial will be carried out in academic settings: the First Affiliated Hospital of Chengdu University of Traditional Chinese Medicine and the Third Affiliated Hospital of Chengdu University of Traditional Chinese Medicine. The flow is shown in Fig. 1.

**Fig. 1 Fig1:**
[figure not shown]
Flow chart of the trial

Before inclusion, participants will be screened in the aforementioned research centers. If the participants meet the inclusion criteria and agree to participate, they will be asked to sign the informed consent form and, then, will be randomized into the electroacupuncture plus clomiphene citrate group (EA group) or the clomiphene citrate group (CC group).

After randomization, the participants will go through a total treatment period of three menstrual cycles. Outcome measurements will be assessed by assessors, blinded to the group assignment, at baseline and the end of treatment. Adverse events will be recorded for the assessment of safety. In addition, a quality monitoring board will be set up to control the quality of the protocol implementation.

The study protocol has been reviewed and approved by local institutional review boards and ethics committees. It follows the principles of the CONSORT and STRICTA statements as well as the Declaration of Helsinki (Sixth revision, 2008). Informed consent will be obtained from all participants.

### Ethics approval

All trial procedures place the participant’s benefit as the highest priority. The present study protocol has already been ethically approved by the Sichuan Regional Ethics Review Committee on Traditional Chinese Medicine with the ethical approval identifier 2015KL-009.

### Participants

We plan to recruit patients with PCOS diagnosed on the basis of *Revised 2003 Consensus on Diagnostic Criteria and Long-Term Health Risks Related to Polycystic Ovary Syndrome* established by The Rotterdam ESHRE/ASRM-Sponsored PCOS Consensus Workshop Group [19]. According to these criteria, women with two out of three of the following items can be diagnosed as having PCOS: (1) oligoovulation or anovulation, (2) clinical and/or biochemical signs of hyperandrogenism, and (3) polycystic ovaries and exclusion of other etiologies (congenital adrenal hyperplasia, androgen-secreting tumors, Cushing’s syndrome). Further assessment of eligibility is based on the inclusion and exclusion criterion as follows.

#### Inclusion criteria

Female, age 20 to 40 yearsDiagnosed as having PCOSSign the inform consent

#### Exclusion criteria

Allergic constitution or allergic to various kinds of medicineHyperandrogenism due to other reasons, including hyperprolactinemia, thyroid disease, congenital adrenal hyperplasia, Cushing’s syndrome, etc.Pathological endometrial changes, such as uterine malformation, hysteromyoma, etc., diagnosed by B ultrasoundGenital tract malformation, gonadal dysgenesis, fallopian tube block, etc.Severe heart, liver, or renal dysfunction or hematological, respiratory, cardiovascular, psychiatric, or other metabolic diseasesWithin 6 weeks post-abortionUse of hormonal or other medication including Chinese herbal prescriptions in the past 3 monthsParticipation in other clinical trials at the same time

### Randomization

In this trial, participants will be randomly assigned to either the EA group or the CC group in a 1:1 ratio using a table of random numbers. The random numbers are generated using SAS statistical software package (Version 9.1, SAS Institute Inc.).

### Blinding

This is an open-labeled trial; therefore, neither the patients nor the clinical practitioners will be blinded for the entire process. However, in order to eliminate potential bias, other researchers, including data collectors and statisticians, will be blinded.

### Interventions

Participants in the EA group will receive electroacupuncture treatment in addition to the oral administration of clomiphene citrate, whereas participants in the CC group will receive clomiphene citrate only. Treatment in both group will last three menstrual cycles. The intervention in this trial involves a rigorous acupuncture schedule. To ensure the compliance of acupuncturists to the schedule, we ask them to take pretrial training and an entrance exam for this trial. All included acupuncturists will have at least 2 years of practical experience in clinical acupuncture.

#### Clomiphene citrate therapy

On the fifth day of menstruation, all participants, except for those with amenorrhea, will receive a pharmacological treatment regimen of 50 mg clomiphene citrate, taken once each day for 5 continuous days. Patients with amenorrhea will receive the same pharmacological treatment regimen after withdrawal bleeding has been induced by taking progestin. In cases of no ovulation, an additional 50 mg will be added to the dose in the next menstrual cycle. The maximum dose will not exceed 150 mg. The therapy will last for three menstrual cycles.

#### Electroacupuncture

In order to increase the reproducibility and internal validity of the trial, electroacupuncture treatment will be applied to PCOS patients. As the stimulation of electroacupuncture can be more quantifiable relative to manual acupuncture, its employment may reduce the risk of bias somewhat. Sanyinjiao (SP 6), Guanyuan (BL 26) Zhongji (CV 3), and Zigong (EX-CA 1) have been chosen for the formula of compulsory acupoints. Additionally, sets of three arbitrary points will be alternately selected according to the phase of the menstrual cycle: Taichong (LR 3) and Taixi (KI 3) will be needled after menstruation; Mingmen (GV 4) and Xuehai (SP 10), during the ovulatory period; and Xuehai (SP 10) and Geshu (BL 17), before the next menstruation.

Each acupoint will be needled using a filiform needle (25–50 mm in length and 0.25 mm in diameter) to achieve a *Deqi* sensation (refers to a sensation of numbness, distension, or electrical tingling at the needling site and might radiate along the corresponding meridian). Then, an auxiliary needle (13 mm in length and 0.18 mm in diameter) will be inserted, 2 mm lateral to the first needle, to a depth of 2 mm without achieving *Deqi*. Electrical stimulation will be applied at every acupoint, with one electrode connected to the filiform needle and the other to the auxiliary needle. This method circumscribes the electrical stimulation nearby, rather than going across the human body surface to cause performance bias. Electrical stimulation will last for 30 min in each acupuncture session. Electroacupuncture treatment will be performed three times per week from the fifth day of menstruation or withdrawal bleeding until before the next menstruation for three menstrual cycles.

### Outcome measurements

#### Primary outcome

The primary outcome will be the ovulation rate.

#### Secondary outcomes

The secondary outcomes will include the dominant follicle rate, mean number of dominant follicles, endometrial thickness, time point of ovulation, follicular size before ovulation, luteinizing hormone (LH) level, estradiol (E2) level, and pregnancy rate.

#### Time points of outcome measurement

Outcomes will be assessed at two time points: baseline and the completion of the treatment. Furthermore, patients will be given some regular tests at baseline, including routine blood tests, liver function test, and kidney function test. The overview of the outcome measurement at the different time points is shown in Table 1.

**Table 1 Tab1:** Trial process chart

Time point	Baseline	Post-treatment
Diagnosis		
Inclusion confirmed	✓	
Informed consent signed	✓	
Body sign	✓	✓
Disease history	✓	
Treatment history	✓	
Comorbidity	✓	✓
Current treatment	✓	✓
Outcome assessment		
B ultrasound	✓	✓
Follicle-stimulating hormone	✓	✓
Luteinizing hormone	✓	✓
Testosterone	✓	✓
Estradiol	✓	✓
Blood HCG	✓	✓
Regular tests		
Routine blood tests	✓	
Liver function test	✓	
Kidney function test	✓	
Data collection and statistical analysis		
Adverse event		✓
Causes of dropout		✓
Safety analysis		✓
Compliance analysis		✓

### Assessment of adverse events

According to previous RCTs, acupuncture may cause several types of adverse events, including subcutaneous hematoma, bleeding, skin bruising, and needle site pain. Among these adverse events, subcutaneous hematoma and bleeding were the most common [20]. Acupuncture-related adverse events, including bleeding, hematoma, fainting, serious pain, local infection, etc., will be carefully recorded in the case report forms.

### Sample size calculation

A previous study indicated that 59 % of women with PCOS ovulated after receiving clomiphene citrate [11]. In this trial, the ovulation rate is expected to be 75 % in the EA group and 55 % in the CC group. Considering a significant level of 0.05 and a power of 0.80, 50 participants in each group are required, as calculated by *t* test in G*Power (Version 3, Institute for Experimental Psychology, Heinrich-Heine-University, Germany). At least 58 participants per group and 116 total participants will be recruited to allow for a 15 % dropout rate.

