### Statistical analysis

A statistician blinded to the whole trial process will perform the statistical analyses using the SAS statistical software package (Version 9.1, SAS Institute Inc.) in the Computer Integrated Manufacturing System. For the evaluation of a curative effect in this trial, the full analysis set (FAS) will be used. The FAS is determined according to an intention-to-treat (ITT) population; all randomized patients who receive at least one treatment session will be included in the analysis set. The per-protocol analysis set (PPS) is defined as the patients who complete the study and do not have major protocol violations. Demographic data and other basic indicators will be analyzed to test the balance of the two groups at baseline. The main indicators and global indicators will be analyzed within the FAS and PPS. The results will be described with mean, standard deviation, median, P25 (percentile 25), P75 (percentile 75), maximum, and minimum values of the differences between the treatment period and the baseline period. Between-group differences will be tested using repeated measure analyses of the variance. The accepted level of significance for all analyses was *P* < 0.05. Considering the influences of other factors on the effectiveness, such as age, duration of disease, etc., these factors will be considered as covariants for the covariance analysis or logistic regression analysis when comparisons are made between the groups. Missing data will be replaced according to the principle of multiple imputations.

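### The stated 50 per group does not follow from 75% versus 55% ovulation at significance 0.05 and 80% power; with one yes/no result per woman it gives about 56% power two-sided (68% one-sided)

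*Protocol article*

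**What the plan says.** All inputs are in the protocol article, under Sample size calculation. One earlier study is cited, in which "59 % of women with PCOS ovulated after receiving clomiphene citrate". For this trial, "the ovulation rate is expected to be 75 % in the EA group and 55 % in the CC group". The conclusion is "Considering a significant level of 0.05 and a power of 0.80, 50 participants in each group are required", attributed to a t test in G*Power. The section gives no standardised effect size, no standard deviation and no sidedness. The dropout step follows: "At least 58 participants per group and 116 total participants will be recruited to allow for a" 15% loss.

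Elsewhere in the article, the primary outcome is the ovulation rate, with no statement of whether it is counted per woman or per cycle (Primary outcome). Allocation is 1:1 (Randomization). Outcomes are assessed at baseline and at completion of treatment (Time points of outcome measurement). For the comparison of groups, "Between-group differences will be tested using repeated measure analyses of the variance" (Statistical analysis).

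**The concern.** The article gives two rates, a significance level, a power and an allocation ratio. For a binary outcome these fix the sample size up to sidedness and the choice of formula, so the 50 can be checked directly. It is far below what any standard formula returns.

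This is the only justification of the trial's size, and it concerns the only primary outcome. If the true power is near 56%, the chance of missing the planned 20-point effect is about 44%, not the 20% implied. A non-significant result would then be read as coming from a trial with 80% power, and so as stronger evidence against electroacupuncture than it is.

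**Working it through.** **Inputs.** p1 = 0.75, p2 = 0.55, significance 0.05, power 0.80, stated n = 50 per group, 15% dropout, 58 recruited per group (all from Sample size calculation); 1:1 allocation (Randomization). Sidedness is not stated. Two-sided is taken as the main case because the planned between-group test is an analysis of variance, whose F test is non-directional; one-sided results are shown beside it.

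**1. Attempt to reproduce 50 with two proportions.** The mean rate is 0.65.

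n = [z_α √(2 × 0.65 × 0.35) + z_β √(0.75 × 0.25 + 0.55 × 0.45)]² / 0.20²

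- Two-sided: (1.96 × 0.6745 + 0.8416 × 0.6595)² / 0.04 = (1.3221 + 0.5551)² / 0.04 = 88.1, so **89**.
- One-sided (1.645 in place of 1.96): 69.3, so **70**.
- Other formulas, two-sided: 86 (unpooled), 88 (arcsine), 98 (continuity-corrected). One-sided: 68, 69 and 79.

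None gives 50.

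**2. Attempt to reproduce 50 with a t test, the method named.** The standard deviation implied by the rates is √[(0.1875 + 0.2475)/2] = 0.466, so d = 0.20/0.466 = 0.43. The noncentral t calculation gives 86.3, so **87** two-sided, and 67.9, so **68** one-sided. This is nearly the same as step 1.

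**3. What would give about 50.** A t test returns about 50 for d = 0.566 two-sided (50.03) or d = 0.5 one-sided (50.15). Neither is the d = 0.43 that the stated rates imply for a binary outcome.

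**4. Power actually available for 75% versus 55%.**

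| Evaluable per group | Two-sided | One-sided |
|---|---|---|
| 50 | 55.6% | 67.8% |
| 58 (no dropout) | 62.0% | 73.5% |

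Exact enumeration at 50 per group, two-sided, gives 55.8% for the chi-square test and 47.7% for Fisher's test.

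**5. Effect detectable with 50 per group.** Holding the clomiphene rate at 55%, the step 1 formula for 81% versus 55% gives 49.3, so 50. The difference detectable with 80% power, two-sided, is therefore about 26 points.

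**6. Sensitivity to the control rate.** For 75% versus 59%, two-sided, n = 134.4, so 135 per group. Power at 50 per group is about 40%.

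**7. Dropout step.** 50 / 0.85 = 58.8, so 59. The stated 58 matches 50 × 1.15 = 57.5 rounded up, and 58 × 0.85 = 49.3.

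**The case against.** The best defence is that ovulation may be meant as each woman's proportion of ovulatory cycles over three cycles. Treatment lasts three cycles, and the clomiphene rule refers to whether ovulation occurred in the previous cycle, so the information must exist cycle by cycle. A t test would then be a natural choice. With within-woman correlation r, the standard deviation of a woman's mean is 0.466 × √[(1 + 2r)/3]. At r = 0.36 this is 0.353, so d = 0.20/0.353 = 0.566 and 50 per group has 80% power two-sided. Power would be about 87% at r = 0.2, 74% at r = 0.5 and 56% at r = 1.

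The arithmetic is sound, and it means the documents do not prove that the design lacks 80% power under every definition of the outcome. But the article states neither a per-cycle unit nor a correlation, and its assessment schedule lists only baseline and end of treatment. The reading is possible but not documented.

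Four stronger inferences should also be resisted:

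- **That the t test caused the shortfall.** Step 2 shows it moves n by only about two per group.
- **That a one-sided d = 0.5 was entered.** It fits, but so does d = 0.566 two-sided; the article does not say.
- **That 55% is an error because the cited rate is 59%.** The article discloses both and adopts 55% as its own expectation. The lower rate widens the planned difference from 16 to 20 points without explanation, which justifies a sensitivity scenario and no more.
- **That the trial has roughly an even chance of missing its effect.** That takes the low end. Two-sided, the chance is about 44% at 50 per group and 38% if all 58 are evaluable.

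**Conclusion.** The sentence is wrong as written: 50 per group does not follow from the inputs beside it. With one yes/no result per woman, the requirement is 89 per group two-sided or 70 one-sided. The power at 50 is about 56% or 68%, and no sidedness reaches 80% even with all 58 evaluable.

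The size of the shortfall rests on two assumptions. The outcome is taken as binary per woman, and the headline 56% is for a two-sided test. Relaxing the second does not rescue the figure. Relaxing the first could, but only with a correlation of about 0.36 or lower, which the article does not give. The cause can be located only in the unstated effect size or standard deviation. The dropout slip is a side note worth less than one evaluable woman per group.

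**What to change.** Replace the sentence with a two-proportion calculation that states its sidedness. It should report that 50 evaluable per group gives about 56% two-sided power for 75% versus 55%, and 80% power only for a difference of about 26 points (55% versus 81%). Show 75% versus 59% as a sensitivity scenario, with about 40% two-sided power at 50 per group.

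If the 50 was in fact based on a per-woman rate over three cycles, say so in the primary outcome definition and in the sample size section, and give the standard deviation and the assumed within-woman correlation (about 0.36 would be needed for 80% power).

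Correct the dropout line to 59 per group, or keep 58 and state that it leaves about 49.

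This is a rewording of one paragraph. It requires no increase in enrolment, apart from one woman per group if 59 is chosen. The cost is a less favourable stated power. The article reports that the trial had not begun at submission, so if the sponsor prefers to keep 80% power for a binary outcome, 89 / 0.85 = 104.7, so 105 per group, would be the two-sided figure; that is a separate decision.

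### Minor: 58 women per group do not allow for 15% dropout from a required 50 per group (58 × 0.85 = 49.3); they allow for about 13.8%

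*Protocol article*

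**What the plan says.** The section "Sample size calculation" of the protocol article sets the size in two steps. The base figure comes first: "Considering a significant level of 0.05 and a power of 0.80, 50 participants in each group are required". The dropout margin follows: "At least 58 participants per group and 116 total participants will be recruited to allow for a" dropout rate of 15%. The abstract gives the same total of 116, allocated 1:1.

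The section "Statistical analysis" evaluates the treatment effect in the full analysis set, for which "all randomized patients who receive at least one treatment session will be included in the analysis set". It also analyses the main indicators in a per-protocol set, "defined as the patients who complete the study and do not have major protocol violations", and replaces missing data by multiple imputation.

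**The concern.** A dropout rate is ordinarily a share of those who enter the trial. A recruitment target that allows for 15% dropout should therefore still leave the required number after 15% of the recruits are lost. The target of 58 per group does not quite do so. It looks as if 15% was added to the required number, when the required number should have been divided by 0.85.

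What is at stake is whether a stated design figure is correct, since the sentence claims a protection that the target falls just short of giving. The practical effect on the trial is very small. The same formula would, however, carry a larger absolute gap into any larger base figure.

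**Working it through.** **Inputs**, all from "Sample size calculation": required n = 50 per group; dropout d = 0.15; recruited 58 per group, 116 in total.

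**1. Reproducing the plan's figure.** n × (1 + d) = 50 × 1.15 = 57.5, rounded up to 58 per group and 2 × 58 = 116 in total. This matches exactly. The article does not print its formula, so this origin is inferred from the match.

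**2. What 58 leaves after 15% loss.**
- Per group: 58 × 0.85 = 49.3, below 50.
- Total: 116 × 0.85 = 98.6, below 100.

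**3. What 15% loss among recruits requires.** n / (1 − d) = 50 / 0.85 = 58.8, rounded up to 59 per group and 118 in total. Check: 59 × 0.85 = 50.15, which meets 50.

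**4. The loss that 58 tolerates.** 1 − 50/58 = 8/58 = 0.138, or 13.8%.

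**5. Effect on power.** The article names a t test but gives neither the standardised effect nor the sidedness, so I took the effect size at which 50 per group gives exactly 80% power at the 0.05 level and recalculated with the noncentral t distribution.

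| | Effect size giving 80% at 50 | Power at 49.3 | Power at 49 |
|---|---|---|---|
| Two-sided | 0.566 | 79.4% | 79.2% |
| One-sided | 0.501 | 79.5% | 79.3% |

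The loss is about 0.5 to 0.8 percentage points. A two-proportion calculation at the stated 75% and 55% (two-sided 0.05) gives 55.6% power at 50 per group and 54.7% at 49. The level is much lower there, which is a separate question about the base figure, but the change from one woman fewer per group is again under one point.

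**6. How the formula scales.** For illustration, the two-proportion formula at 75% versus 55% (two-sided 0.05, 80% power) gives 89 per group. Then 89 × 1.15 = 102.35, rounded up to 103, while 89 / 0.85 = 104.7, rounded up to 105. The gap becomes two women per group.

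**The case against.** The best case against raising this is that it is close to rounding. The shortfall is 0.7 of a woman per group, and 116 against 118 is a difference of 2 in 118, or 1.7%. The target is worded as a minimum, which 59 would satisfy. The 15% is itself a planning guess, and the tolerated 13.8% differs from it by only 1.2 points. The base figure of 50 also does not follow from the stated rates by a two-proportion calculation, so adjusting the margin on top of it does not repair the sizing.

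Most of this stands, and it is why the point is minor. It does not make the sentence right: the minimum is itself presented as what allows for 15% dropout, and that minimum falls short. The question about the base figure is separate and does not correct the dropout step.

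A reader might go further and infer that the allowance removes women whom the full analysis set keeps, or that the sizing describes completers only. The article supports neither:
- The allowance removes nobody from the analysis; it adds recruits to offset lost outcome information. That fits a full analysis set with multiple imputation, because imputation does not restore missing information. Women who receive no session leave that set, and non-completers leave the per-protocol set.
- The 75% and 55% are given as expected rates in the two groups and are nowhere described as rates among completers.

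A reader might also infer a material loss of power from women who stop electroacupuncture and then ovulate at the control rate. That needs assumptions about how many stop, whether their outcomes are observed and how far they revert, and the article gives none of these.

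**Conclusion.** The point holds as a minor correction. The statement that 58 per group (116) allows for 15% dropout from a required 50 per group is wrong as written: 15% loss leaves 49.3 per group, and 58 tolerates 13.8%. The discrepancy is one woman per group, two in total, and under one percentage point of power.

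This rests on reading the dropout rate as a share of those recruited, and on taking the 50 per group as the article states it, without endorsing that figure. The finding is confined to the dropout step and implies no conflict with the choice of analysis sets.

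**What to change.** Restate one sentence in "Sample size calculation" in either of two ways:
- 58 per group (116 in total) allows for about 13.8% dropout; or
- with 58 per group recruited, 15% dropout would leave about 49 per group.

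Either wording keeps the target of 116 and needs no change in conduct. For reference, holding both the 15% and the 50 would correspond to 59 per group and 118 in total. If the base figure of 50 is revised for any reason, the new figure should be inflated as n / (1 − dropout rate).

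The cost is one edited sentence and a slightly less favourable stated margin. The article reports that the trial had not begun at submission.
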